### Intervention

2.5

There will be two groups involved in this study, as follow.

#### Mobile health intervention group

2.5.1

Health education in the mobile health intervention group will be delivered via the WeChat platform on smartphones. The physician or nurse will use WeChat’s messaging function to communicate with the patient promptly. The physician or nurse will address the patient’s concerns promptly. The physician or nurse can also intervene in patient care promptly through the WeChat platform (49).

To ensure high-quality delivery of the intervention, the professionals involved in delivering health education through WeChat (physicians and nurses) will need to meet the following criteria:

Physicians must hold a valid medical degree in general practice or a relevant specialty and have at least 2 years of experience in patient care.Nurses must be licensed and have at least 1 year of experience in patient education or health promotion.All professionals must undergo a brief training program on the HAPA model, the principles of mobile health interventions, and effective communication through digital platforms like WeChat.

##### Pre-intentional stage

2.5.1.1

At this stage, patients have not yet developed a willingness to improve health behaviors or engage in functional exercises.

###### Action self-efficacy

2.5.1.1.1

(1) Purpose: to help patients develop initial self-efficacy and motivation to change their health behaviors.(2) Measures: each patient will receive a booklet titled “Health Education for Patients with Brucellosis.” While distributing the booklet, the physician will explain common issues, encourage a positive approach to the disease, and guide patients to actively improve their health behaviors (31). During the initial consultation, physicians will add patients’ WeChat contact information and categorize them for follow-up health education. For patients with low health awareness, physicians will promptly discuss reasons for the lack of awareness, help identify solutions, and encourage mutual communication between patients and physicians.

###### Expected outcomes

2.5.1.1.2

(1) Purpose: to provide patients with an initial understanding of brucellosis and its later stages.(2) Measures: physicians will provide one-on-one re-education to patients via WeChat, based on a self-designed push program and the brochure “Health Education for Brucellosis Patients” (50). The push program includes scientific articles on brucellosis-related concepts, disease processes, and case studies. The focus is on the negative outcomes of advanced brucellosis and the benefits of effective disease management. The program also emphasizes the importance and effectiveness of adopting healthy behaviors for better outcomes.

###### Risk perception

2.5.1.1.3

(1) Purpose: to enhance patients’ risk perception and foster a willingness to engage in positive health behaviors.(2) Measures: physicians will push scientific articles on the disease process to patients via WeChat, based on the “Health Education for Brucellosis Patients” manual and a self-designed push program. The push program includes case studies to emphasize the dangers of brucellosis and its potential adverse outcomes (51). Additionally, the importance of forming healthy behaviors and their effectiveness in improving outcomes was emphasized. For patients with low health beliefs, the emphasis will be on the harmful effects of brucellosis on productivity and the benefits of controlling the epidemic.

##### Intent stage

2.5.1.2

###### Action plan

2.5.1.2.1

(1) Purpose: enhance patients’ self-efficacy for maintenance(2) Measures: patients will receive 10-min health guidance from the physician via WeChat every Monday. The physician will help patients develop a long-term health behavior improvement plan and provide daily reminders via WeChat. The content of health education topics will be based on multimedia, in the form of articles, pictures, or videos sent to the advance WeChat group. For patients with low adherence, physicians will emphasize the dangers of neglecting animal husbandry hygiene, the risks of infectious diseases, and the benefits of maintaining hygienic habits and adhering to medication schedules. For patients with moderate adherence, physicians will focus on praise and encouragement to help maintain their confidence. For patients with high adherence, physicians will focus on monitoring their progress. Physicians will proactively seek recovery progress from all patients, guide them on the correct use of medication, and encourage active cooperation in treatment. The physician will encourage all patients to fill out the “Health Behavior Diary,” documenting daily health behaviors, issues, and experiences encountered. Patients will also be encouraged to communicate with the physician promptly, and their health behavior progress will be regularly evaluated.

###### Response plan

2.5.1.2.2

(1) Purpose: to maintain patient self-efficacy by addressing challenges encountered during treatment.(2) Measures: healthcare workers are essential in guiding patients who are livestock farmers towards successful recovery. Patients are encouraged to prioritize their recovery and are informed about the risks associated with their condition. Additionally, their families will be educated to increase awareness of the disease. Tailoring healthcare guidance to patients’ lifestyle habits is essential. Furthermore, collaborating with and seeking the supervision of their families is crucial. Addressing irregular medication intake is critical, as healthcare workers engage both patients and their families in discussions. Analyzing the reasons for inconsistent medication practices allows healthcare workers to encourage and acknowledge patients’ efforts to adopt healthier behaviors. In cases where patients show negative emotions and stop treatment-related health behaviors, promptly analyzing the reasons is essential. Appropriate strategies should be developed to help patients self-regulate their emotions, facilitating a swift resumption of health behaviors if interrupted (52).

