**Figure 1 fig1:**
[figure not shown]
Schematic diagram of health action process approach.

To date, no research has focused on the application of the HAPA model in the health management of brucellosis patients. Therefore, applying the HAPA model in the health management of brucellosis patients could significantly contribute to improving their health behaviors.

This study aims to develop a health education intervention model for brucellosis patients based on the HAPA framework. The first step involves assessing the current level of knowledge regarding brucellosis among patients. Drawing from best practice evidence, brucellosis-related information will be integrated to design a personalized health management intervention program for patients. The intervention will be delivered through the WeChat platform and mobile health devices, utilizing doctor-patient interaction for interactive health education. The goal is to deliver lifestyle-based behavioral interventions to assist patients in developing self-management habits.

The intervention tested in this trial will be based on the Health Action Process Approach (HAPA) model, which incorporates behavior change processes such as self-efficacy, risk perception, and the formation of action plans. This theoretical framework will guide the development and delivery of mHealth-based interventions, ensuring that the intervention is rooted in behavioral science to improve health outcomes in brucellosis patients. By integrating multimedia content and offering continuous support through mobile health devices, the intervention aims to enhance patient engagement and improve long-term self-management behaviors. The control group will receive usual care, which does not include mHealth interventions based on behavior change models. Usual care for brucellosis patients typically involves standard medical treatment, such as general health education, but lacks structured mHealth behavioral interventions. The choice of usual care as the comparator is justified by the absence of structured mHealth behavioral interventions for brucellosis. Since no established mHealth interventions are available for brucellosis, the comparison with usual care, which does not include a behavior change intervention, is the most appropriate to evaluate the effectiveness of the proposed intervention.

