### Sample size

2.4

This study is a randomized controlled trial with two groups: the mobile health intervention group and the conventional education group. The primary outcome is the health behavior formation rate among the participants. Based on a literature review (48), the compliance rate for behavior formation in the mobile health intervention group is expected to be 90%, compared to 60% in the control group. The significance level is set at *α* = 0.05, with a 90% confidence level. Using PASS15 software, the sample size for the intervention group was calculated as N1 = 23, and for the control group, N2 = 23. Considering a 20% follow-up loss rate, at least 29 participants are required in each group, resulting in a total of 58 participants.

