##### Proportion of individuals adopting health behaviors

2.8.1.1

The health behavior was assessed using a self-designed health behavior scale, which consists of five domains: (1) frequency of personal protective measures during contact with livestock (5 items), (2) frequency of personal protective measures when handling lambs and aborted materials (5 items), (3) frequency of personal protective measures when vaccinating livestock (5 items), (4) frequency of cleaning measures when cleaning animal pens (3 items), and (5) frequency of hand hygiene maintenance after contact with cattle, sheep, their placental tissues, or meat products (4 items). Each item was rated on a 5-point Likert scale: “Never (0),” “Rarely (1),” “Sometimes (2),” “Often (3),” and “Almost Always (4).” One reverse-scored item was included in each domain. The total score ranges from 0 to 110, with higher scores indicating better health behavior.

This scale was developed to evaluate the frequency of health behaviors related to occupational safety and hygiene practices among individuals at risk for brucellosis.

The proportion of individuals adopting health behaviors is calculated by determining the proportion of participants who meet the health behavior standard, as assessed by the health behavior questionnaire. A threshold score will be established to determine whether an individual has adopted health behaviors, with a score above 70 considered indicative of good health behavior formation. The adopting proportion is then calculated by dividing the number of individuals exceeding this threshold by the total number of participants.

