### Statistical analysis

2.9

Statistical analyses will be performed using SPSS Statistics 26.0 software. Count data will be expressed as the number of cases and rate (%), while measurement data will be presented as mean ± standard deviation. Before performing parametric tests, normality assumptions will be tested using the Shapiro–Wilk test. If data is normally distributed, parametric tests, such as the independent *t*-test, may be used. However, if the normality assumption is violated, non-parametric tests, such as the Mann–Whitney U test, will be used to compare changes in scale scores between baseline and endpoint between the two groups. The Wilcoxon signed-rank test will be employed for within-group comparisons of scale scores between baseline and endpoint. Demographic and clinical characteristics at baseline will be summarized descriptively for each group. Categorical variables will be reported as counts and percentages, and continuous variables as mean ± standard deviation.

For the primary analysis, all randomized participants will be included in an intention-to-treat (ITT) analysis, regardless of whether they complete the intervention. For secondary analyses, only participants who complete the intervention and follow-up will be included in a per-protocol (PP) analysis.

Regarding missing data, we will explore the missing data and compare the distribution of key variables. If the missing data is reasonable in amount and assumed to be Missing at Random (MAR), multiple imputation methods will be used to handle the missing data for both ITT and PP analyses. This ensures that the handling of missing data is consistent across both analysis groups. Baseline variables will be used as auxiliary variables for imputation, and multiple imputed datasets will be generated. Linear regression and logistic regression will be applied to analyze the imputed datasets, and the results will be pooled to provide final estimates and standard errors. A two-sided test will be used, and statistical significance will be defined as *p* < 0.05. The detailed statistical analysis plan for this study is available for public access at the Chinese Clinical Trial Registry: ChiCTR Statistical Analysis Plan (https://www.chictr.org.cn/showproj.html?proj=196659).

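### The mHealth arm educates patients' families, yet nothing stops two patients from one household or livestock holding from being randomised to opposite arms, so a control could receive part of the intervention

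*Protocol article*

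**What the plan says.** **Intervention.** Section 2.5.1.2.2 (Response plan), within the mHealth arm, says of patients' families: "Additionally, their families will be educated to increase awareness of the disease". It continues: "Furthermore, collaborating with and seeking the supervision of their families is crucial". Families are also brought into discussions about irregular medication.

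**Comparator.** The Introduction states: "The control group will receive usual care, which does not include mHealth interventions based on behavior change models". Section 2.5.2 shows that usual care is active: discharge education, a brochure and telephone follow-ups. Section 2.4 sizes the trial against this conventional education group. Adoption in "the mobile health intervention group is expected to be 90%, compared to 60% in the control group".

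**Allocation and eligibility.** Section 2.2 randomises individual participants from one Excel list at one hospital, with convenience sampling. It states no household unit or stratum. The only family-related criterion in 2.3.1 and 2.3.2 concerns being reachable and having a family contact.

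**Primary outcomes.** The behaviour scale (2.8.1.1) scores protective measures with livestock, hand hygiene and "frequency of cleaning measures when cleaning animal pens (3 items". The second primary outcome (2.8.1.2) is knowledge of brucellosis.

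**The concern.** The trial is meant to compare the mHealth programme with care that contains no behaviour-change intervention. One part of the programme is aimed at the patient's family, and a family member can also be a trial participant. The Introduction and Discussion attribute infection mainly to contact with infected animals and their products, so people working the same animals share the exposure. More than one of them could reach the same hospital as a patient.

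If two such patients are enrolled and split between the arms, the control is a member of a family that the mHealth arm sets out to educate. Both primary outcomes are open to this. Livestock hygiene is practised jointly on a holding, and disease knowledge is what the family education targets. The effect would be to shrink the estimated difference.

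Household members are also likely to answer alike, whichever arm they are in, while the tests in 2.9 assume independent participants.

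**Working it through.** **1. Is the route open?** Three statements have to hold together.
- Family education and supervision belong to the mHealth arm: yes (2.5.1.2.2).
- Allocation is by individual, with no household unit: yes (2.2).
- No eligibility rule limits enrolment to one person per household or holding: correct. Both lists are given in full (2.3.1, 2.3.2).

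The route is therefore open. Whether anyone takes it is not documented.

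**2. Inputs for size.** Adoption rates of 90% and 60%, 23 per arm before dropout and 29 per arm randomised (2.4); two-sided test at 0.05 (2.9). The number of exposed controls, k, is not in the documents and is assumed.

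**3. The plan's own figure.** The dropout step reproduces: 23 / 0.8 = 28.75, so 29 per arm and 58 in total. The 23 does not. Section 2.4 gives "0.05, with a 90% confidence level" and names no power. Reading the 90% as power, the pooled two-proportion formula at two-sided 0.05 gives 42 per arm; at 80% power it gives 32. A figure of 23 appears with one-sided 0.05, 80% power and the unpooled formula (22.67, rounded up). That is a separate and larger matter. Here it only means that the trial has little power to spare.

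**4. Dilution.** If k of 29 controls are exposed and each reaches 90%, the control rate is

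p_C = 0.60 + (k/29) × (0.90 − 0.60).

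If they gain half the effect, 0.30 is replaced by 0.15. Power is by exact enumeration of two binomials with a two-sided pooled z-test at 0.05 and 29 per arm.

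| Exposed controls k | p_C, full effect | Power | p_C, half effect | Power |
|---|---|---|---|---|
| 0 | 60.0% | 77.8% | 60.0% | 77.8% |
| 1 | 61.0% | 75.3% | 60.5% | 76.6% |
| 3 | 63.1% | 69.8% | 61.6% | 74.0% |

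One fully exposed control costs 77.8 − 75.3 = 2.5 points and three cost 77.8 − 69.8 = 8.0 points. With half the effect the losses are 1.2 and 3.8 points. The expected difference falls from 30 points to 29.0 with one fully exposed control and to 26.9 with three.

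With 23 per arm, power is 68.9% with no exposure and 61.2% if 10% of controls are fully exposed, a similar loss of about 8 points. The normal-approximation formula gives 66.1% and 58.3%, again about 8 points.

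**5. How many pairs would that take?** With 1:1 allocation of 58, a given pair is split with probability 29/57 = 0.51. Three exposed controls therefore need about 3 / 0.51 ≈ 6 co-enrolled pairs, that is 12 of the 58 participants. One exposed control needs about two pairs.

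**6. Second primary outcome and clustering.** Section 2.4 gives no rates for knowledge, so only the direction can be stated: towards no difference. For clustering, the documents give neither the number of pairs nor a correlation, so no size can be given.

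**The case against.** Several points on the other side stand.

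- A reader might infer that the mHealth programme itself is delivered to families. It is not. Families receive disease-awareness education, a supervisory role and a part in medication discussions. The weekly WeChat guidance, daily reminders, action plan and diary in 2.5.1.2.1 are for patients. An exposed control would receive one component, so reaching 90% is an upper case.
- A reader might infer that the 60% control rate describes untreated patients. Section 2.4 sizes against conventional education, and 2.5.2 already gives controls a brochure and telephone contact. Some disease information is in both arms, so the extra exposure is smaller.
- A reader might conclude that the comparator has ceased to be usual care. That would need co-enrolled and split pairs, and the documents report none. With 29 controls the number may be zero. Exposure of 17% to 20% of controls (five or six) would need about 10 to 12 pairs, or 20 to 24 of the 58 participants, which nothing in the documents supports.
- The general exclusion criterion 7 in 2.3.2 would let an investigator decline a relative.

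The last point does not close the gap, because discretion is not a rule and nothing prompts the investigator to ask. The other three limit the size of the problem. They do not remove the open route or change the direction of the bias.

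**Conclusion.** The concern holds as a conditional weakness. The protocol makes family education and supervision part of one arm, randomises individuals, and leaves patients from the same household or holding free to be allocated to opposite arms. If that occurs, the affected controls receive part of the family component, both primary comparisons are pulled towards no difference, and the independence assumed by the tests fails.

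The size is probably small and cannot be fixed from the documents. Power at 29 per arm goes from 78% to 75% with one exposed control and to 70% with three, if each gains the full effect; the loss is about half as large with half the effect. These figures rest on an assumed number of exposed controls and an assumed gain. They are illustrations, not estimates. The protocol does not contradict itself here, and the text does not show that contamination will happen. This is a cheap improvement.

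**What to change.** Add to 2.3.2 an exclusion for any patient whose household or shared livestock holding already has an enrolled participant. Check it with one new question at screening. Criterion 1 cannot supply the answer, because it establishes only that the patient can be reached and has a family contact.

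If pairs are already enrolled, flag them and keep the intention-to-treat analysis as it stands. Repeat the primary analysis as a sensitivity analysis that excludes any control who shares a household with an mHealth participant. Dropping whichever member enrolled later would not do: where the control enrolled first, the exposed control would stay in and the mHealth partner would be lost.

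The cost is one eligibility line, one screening question and, if needed, one extra analysis. A few otherwise eligible relatives could not be enrolled, which may slow recruitment slightly.

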#### Control group

2.5.2

In the control group, patients will receive the standard discharge education provided upon their discharge from the hospital. As part of this education process, patients will be given a “Brucellosis Health Education” brochure, which contains essential information about brucellosis, including lifestyle recommendations, dietary guidelines, medication instructions, and potential adverse reactions to be aware of. Following discharge, patients will receive a telephone follow-up within a specified period, and an additional follow-up will take place 3 months post-discharge (53). These follow-ups are intended to assess patient progress, adherence to instructions, and any emerging concerns related to their condition.

#### Regulations on participation adjustment for interventions

2.5.3

During the implementation of the health education program, participants retain the right to voluntarily withdraw from the study at any time. The research team will suspend or modify intervention measures under the following circumstances:

(1) Participant-initiated withdrawal due to personal reasons;(2) Termination requested by the participant or legal guardian based on health or privacy concerns;(3) Emergence of health-related unexpected issues during the intervention (e.g., sudden illness or exercise-related injuries);(4) Research team-determined suspension based on safety evaluations.

All withdrawal requests and intervention adjustments must be fully documented in case report forms, including reasons for withdrawal, communication details, follow-up measures, and strict adherence to ethical review requirements for participant privacy protection.

### Plans to promote participant retention and complete follow-up

2.6

To promote participant retention and ensure complete follow-up, the following strategies will be implemented:

(1) Regular reminders: participants will receive regular reminders via phone calls, text messages, or emails about upcoming visits and follow-up appointments.(2) Telephone contact: in addition to scheduled visits, the research team will maintain regular telephone contact with participants to address any concerns, remind them about the study requirements, and ensure continued participation.(3) Incentives: participants will be offered small incentives (e.g., transportation reimbursement or gift cards) to encourage retention and timely follow-up.(4) Data collection for dropouts: if participants discontinue or deviate from the intervention protocol, efforts will be made to collect their data, including interviews and questionnaires, to minimize bias and understand reasons for discontinuation.

